### Randomisation and blinding

All patients and their direct relatives will be informed regarding the intentions and technological procedures involved in the study at the time of hospitalisation. Written informed consent will be obtained following patient agreement. The sealed envelope system will be used for randomisation of the patients into two groups. The envelope will be supported by a recognised third-party organisation. Neither the investigator nor the participants will be aware of each envelope’s contents.

Clinicians will know the exact allocation of each patient, and blinding will not be performed. In addition, patients will not be blinded due to the differences between the treatment strategies. Patients will also provide written informed consent the day prior to surgery.

### Statistical analysis

In the present study, we aim to compare treatment outcomes between two different surgical strategies for mTLE. Kaplan-Meier estimator will be conducted to compare the seizure outcome between two groups at 3, 6, and 12 months’ interval. Cognitive function, visual field defects, and Engel class I outcomes will be compared between the groups using χ^2^ tests or t tests. Subgroup analysis will be made if the results are positive. Average complication rate and hospitalisation expenses will be qualitatively compared between the two groups. For each separate group, a logistic analysis will be made to further explore the factors which may affect the outcomes (p < 0.05). Statistical analysis will be performed using SPSS version 21 (SPSS Inc., Chicago, IL, USA) and/or MATLAB_R2018a (MathWorks Inc., Natick, MA, USA).

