**Fig. 1 Fig1:**
[figure not shown]
Timeline of the STARTS protocol. Patients assigned to the ATL group will undergo ATL directly. Patients assigned to the RF-TC group will undergo SEEG implantation and monitoring until the first seizure episode. Then, 3D-crossing RF-TC will be conducted

Patients enrolled in arm 1 will undergo open ATL following pre-surgical evaluation, which will be conducted as established by Wiebe et al. in their RCT for mesial temporal lobe epilepsy [4]. Two experienced neurosurgeons will perform ATL for mTLE and resection will be 5.5 cm on the non-dominant hemisphere or 4.5 cm on the dominant hemisphere, as referenced in Wiebe et al. [4]. The mesial part of the resection will include the ipsilateral amygdala, hippocampus, and uncinate gyrus. The full procedure will be recorded by the neurosurgeons performing the resection. Patients will continue taking the same AEDs that they had been taking prior to surgery under the supervision of a neurologist. Patients will not stop AED treatment until the 1-year follow-up even if they do not experience seizures.

Patients enrolled in arm 2 will undergo SEEG implantation and RF-TC for mTLE. SEEG implantation will be performed following pre-surgical evaluation. The target points of the SEEG electrodes will cover the mesial part of the ipsilateral temporal region. Both long-axis and parallel vertical depth electrodes generating a 3-dimensional space will be designed to guide RF-TC in cases of small ablation volume (Fig. 2). For each patient, bipolar coagulation will be performed on each of two contiguous contacts of the longitudinal and vertical electrodes using the same parameters. Contacts between electrodes will be further coagulated at intervals of < 5 mm to ensure freedom from vascular injury. This modified approach provides extended volume including the amygdala, hippocampus, subiculum, and part of the entorhinal cortex (Fig. 2). Similarly, patients will not stop taking AEDs until the 1-year follow-up.

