### Outcomes

The primary outcome measure is cognitive function after treatment, which will be assessed using the Chinese version of the full-scale Wechsler Adult Intelligence Scale-IV (WAIS-IV-C) for adults (> 16 years old) or the Chinese version of the Wechsler Children’s Intelligence Scale-IV (WCIS-IV-C) for children. Assessments will be performed before and 1 year after surgery. Higher values are considered indicative of better outcomes.

Secondary outcomes are as follows:
Post-surgical seizure outcomes after 1 year based on Engel classification. Engel 1A and 1B will be considered to reflect seizure freedom, while Engel 1C–4 will be considered to reflect seizure recurrence. Seizure outcomes will be assessed at 3, 6, and 12 months via telephone interviews or outpatient visits with the patient and direct relatives. Seizures occurring within the first 2 weeks after surgery will not be considered to reflect seizure recurrence.Visual field examination results: We will compare the number of patients with visual field defects between arm 1 and arm 2 before and 1 year after surgery.The number of participants with procedure-related complications 1 year after surgery, including postoperative stroke with or without symptoms (via MRI), postoperative intracranial bleeding with or without symptoms (via MRI), postoperative intracranial infection, postoperative wound infection, and postoperative subcutaneous dropsy.Quality of life after treatment. Values will be assessed using the Quality of Life in Epilepsy-89 scale (QOLIE-89) for adults (age 17–60) and the Quality of Life in Epilepsy-48 scale (QOLIE-48) for children (age 14–16) 1 year after surgery.Average hospitalisation expenses 1 month after surgery.

All clinical and outcome-related data will be collected by two experienced clinicians (one neurologist and one neurosurgeon). Detailed data collection and follow-up timeline are shown in Table 1. For each patient, a case report form (CRF) including comprehensive patient information, clinical data, scale results, and outcomes will be completed.

**Table 1 Tab1:** Data collection

Assessment	Baseline	Follow-up 7 ± 2 days	Follow-up 90 ± 7 days	Follow-up 180 ± 7 days	Follow-up 360 ± 14 days
Informed consent	□				
Demographics	□				
History of epilepsy	□				
Physical examination	□	□			□
EEG	□		*□		□
AEDs	□	□	□	□	□
Visual field assessment	□				□
WAIS-IV-C/WCIS-IV-C	□				□
QOLIE-89/QOLIE-48	□				□
Engel classification		□	□	□	□
PET	□				
MRI	□	□	*□		□

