### Sample size

The sample size was calculated based on our previous experience (cognitive performance decrease of 25% after ATL), similar to findings reported in earlier studies [18]. Approximately 5% of patients exhibited decreased cognitive performance after SEEG-guided RF-TC in our previous series, while most previous studies have reported improvements or a lack of impairment [20–22]. We expect to enrol 20 patients in each arm using a one-sided 95% confidence interval, a non-inferiority limit of 10%, and an expected withdraw rate of 20%. Thus, we aim to include a total of 40 patients in this trial. Patients will be recruited from outpatient and MDT with strict inclusion criteria.

Participants will be replaced if they withdraw at any time prior to the final follow-up supervised by [name] and [name]. Those who withdraw from the study during treatment because of specific medical or technical events will also be monitored and replaced. The trial conduct will be audited by the investigators with the whole MDT monthly.

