## Discussion

RCTs are considered the most reliable form of scientific evidence given their ability to reduce spurious causality and bias. However, to our knowledge, the present study is the first RCT to compare cognitive outcomes and treatment results between SEEG-guided RF-TC and standard ATL for mTLE.

ATL has been considered an effective treatment for temporal lobe epilepsy and is now the most commonly used surgical technique for mTLE patients. Long-term seizure-free rates for ATL range from 59 to 80% [23]. However, previous studies have reported that ATL for mTLE is associated with complications such as memory impairments and visual field deficits [9, 20]. A systematic review by Sherman et al. noted verbal memory decline in up to 44% and 20% of patients undergoing dominant and non-dominant hemisphere ATL, respectively [24]. Given that SEEG-guided RF-TC may ensure better preservation of cognitive function and reduce the risk of visual field impairments, RCTs evaluating such treatment are required.

SEEG is a minimally invasive method for precisely localising the seizure-onset zone that is advantageous due to its ability for a three-dimensional definition of the epileptogenic zone [25]. Although SEEG-guided RF-TC has been used for typical cases of hypothalamic hamartoma, periventricular nodular heterotopia (PNH), and mTLE with or without hippocampal sclerosis, treatment outcomes have varied across studies, and the efficacy of RF-TC for mTLE remains controversial [13, 14, 16, 18]. Moles et al. compared postoperative seizure outcomes between SEEG-guided RF-TC and ATL, reporting that none of the patients in the SEEG-guided RF-TC group achieved seizure freedom. In contrast, 37 patients (75.5%) in the ATL group were seizure-free 12 months after treatment [12]. In a review of their series, Malikova et al. found that nearly 70% of patients were seizure-free postoperatively, similar to findings in our unpublished study [22]. Given these discrepancies, RCTs are also required to verify the non-inferiority of SEEG-guided RF-TC when compared with ATL.

Limitations of the study include the strict eligibility criteria which may lead the difficulty for the participant enrolment. Secondly, as we focused only on mTLE with hippocampal sclerosis patients, other types of temporal lobe epilepsy (such as neocortical temporal lobe epilepsy) will not be investigated in this study and further research may be promoted.

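### Cognition is to be compared by unadjusted χ² or t tests although baseline full-scale IQ is collected for every patient; adjusting for it would gain precision at almost no cost

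*Protocol article*

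**What the plan says.** The Outcomes section states that "The primary outcome measure is cognitive function after treatment", measured by the full-scale Wechsler instrument for the patient's age, and that "Assessments will be performed before and 1 year after surgery". Table 1 marks the scale as required at baseline and at the 360-day visit, and an IQ above 70 is an entry criterion.

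For the comparison between arms, the Statistical analysis section says: "Cognitive function, visual field defects, and Engel class I outcomes will be compared between the groups using" χ² or t tests. It names no covariate. The only regression mentioned is inside each arm: "For each separate group, a logistic analysis will be made to further explore the factors which may affect the outcomes". That cannot adjust the comparison of one arm with the other.

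The section does not say whether the tested quantity is the 1-year score, the change from baseline or a yes/no decline. The Sample size section plans on proportions. It sets a "cognitive performance decrease of 25% after ATL" against about 5% of patients after RF-TC, with a 10% limit, 20 patients per arm and 20% withdrawal.

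**The concern.** IQ differs far more between people than a treatment is likely to move it. A two-sample test on 1-year scores carries all of that between-person variation, although the baseline score that would remove most of it has already been collected. With 20 per arm, the arms can also differ by several IQ points at entry, and an unadjusted comparison passes part of that difference into the result. At stake are the width of the interval on the primary outcome and how far one reported difference reflects who was allocated where.

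**Working it through.** **1. The plan's own figure.** Inputs from the Sample size section: no decline in 75% (ATL) and 95% (RF-TC), margin 10 points, one-sided 5%, 20% withdrawal. Power is not stated; 80% is assumed.

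n = (0.75×0.25 + 0.95×0.05) × (1.645 + 0.842)² / (0.20 + 0.10)² = 0.235 × 6.18 / 0.09 ≈ 16.1 per arm; 16.1 / 0.8 ≈ 20.2.

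This reproduces the stated 20 to within rounding (rounding up to 17 before inflating gives 22). So the 10% margin is on the proportion who decline, not on IQ points.

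**2. Precision if IQ is analysed as a continuous outcome.** Assumed, because the article gives neither: SD 15 at both times and a baseline-to-1-year correlation r of 0.7 to 0.9. Completers per arm: 20 × 0.8 = 16. The article also says withdrawn patients are replaced, so 20 is shown too.

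Half-width = t × SD × k × √(2/n), with k = 1 for the 1-year score, √(2(1−r)) for change and √(1−r²) for ANCOVA.

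- n = 16: 2.042 × 15 × √(2/16) = 10.8
- n = 20: 2.024 × 15 × √(2/20) = 9.6

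| Analysis | n | r = 0.7 | r = 0.8 | r = 0.9 |
|---|---|---|---|---|
| t test, 1-year score | 16 | 10.8 | 10.8 | 10.8 |
| t test, change | 16 | 8.4 | 6.8 | 4.8 |
| ANCOVA | 16 | 7.7 | 6.5 | 4.7 |
| t test, 1-year score | 20 | 9.6 | 9.6 | 9.6 |
| t test, change | 20 | 7.4 | 6.1 | 4.3 |
| ANCOVA | 20 | 6.9 | 5.8 | 4.2 |

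All widths scale with the SD, and their ratios do not depend on it. The IQ > 70 entry rule may make the SD smaller than 15. At SD 12 and n = 16 (multiply by 0.8), the widths are 8.7 (1-year score), 6.7 to 3.9 (change) and 6.2 to 3.8 (ANCOVA).

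Against the 1-year score, ANCOVA narrows the interval by 1 − √(1−r²), which is 29% to 56%. Against change, the ratio is √((1+r)/2): √0.85 = 0.92 and √0.95 = 0.97, a gain of about 8% down to 2–3%. These formulas ignore the cost of estimating the slope. For a roughly normal covariate that cost is about √(1 + 1/28) = 1.018 at 16 per arm, so at r = 0.9 the gain over change is close to nil.

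**3. Chance imbalance in baseline IQ.** The SD of the baseline difference is 15 × √(2/20) = 4.7 points. The probability of a difference of 5 points or more in either direction is 29% (35% at 16 per arm). With equal SDs, a 5-point imbalance moves the expected difference in 1-year scores by r × 5 = 3.5 to 4.5 points. It moves the difference in change scores by (1−r) × 5 = 1.5 to 0.5 points in the opposite direction. ANCOVA corrects for both.

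**4. If the test is a χ² on decline yes/no,** baseline already enters through the definition of decline. The widths in step 2 then do not apply directly.

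**The case against.** The strongest reply is that the article never says the test is on raw 1-year scores. The sample size points to a decline proportion and IQ is measured twice, so baseline may already be used. This stands. It is not established that the plan ignores baseline, and the 10.8-point width belongs to only one of three open readings. A second reply is that unadjusted tests are valid under randomisation. That also stands: the point concerns precision and imbalance in the realised sample, not type I error. A third is that covariates are often left to the analysis plan. But the article does name the tests, and those tests are unadjusted.

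A reader might go further and argue from hemisphere. The Discussion cites "verbal memory decline in up to 44% and 20% of patients undergoing dominant and non-dominant hemisphere ATL, respectively", so an uneven split of dominant-side patients might seem to shift the decline difference by 5 to 6 points, over half of the 10% margin (0.24 × 0.20 = 4.8; 0.24 × 0.25 = 6.0, for gaps of 20 and 25 points between arms). The documents do not support this:

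- The cited rates are upper figures for verbal memory after ATL. No gradient is given for full-scale IQ.
- The calculation needs the same 24-point gradient under RF-TC. With half the patients dominant-side, a 5% mean decline allows at most 10% against 0%. Keeping the 44:20 ratio gives 6.9% against 3.1%, a gradient of 3.75 points.
- Each arm departs from an even split by only half the gap. The shift is then (0.24 + 0.0375) × 0.10 = 2.8 points, or × 0.125 = 3.5 points: about a third of the margin, and only if IQ behaves like verbal memory.

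Nor is dominance shown to be recorded for everyone. It appears only where "resection will be 5.5 cm on the non-dominant hemisphere or 4.5 cm on the dominant hemisphere", which is the ATL arm, and Table 1 lists no dominance assessment. That the randomisation is unstratified is likewise inferred from silence in a condensed article.

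**Conclusion.** The concern holds in limited form. The stated comparison is unadjusted, baseline IQ is required in every patient, and the trial is small, so an adjusted model is a better choice at almost no cost. Against a t test on 1-year scores the interval would be 29% to 56% narrower; against change scores, about 2–8%. Both figures rest on r of 0.7 to 0.9, which the article does not give, and the widths in points also rest on the assumed SD. No figure is claimed for a χ² on decline. The hemisphere argument justifies operated side as an optional covariate and is not evidence of a large bias. The planned tests should not be called invalid.

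**What to change.** For full-scale IQ as a continuous outcome, specify a linear model of 1-year IQ on arm and baseline IQ. Add operated side (dominant or non-dominant) if it is recorded in both arms, and include any stratification factor that was used. Report the adjusted difference with its confidence interval, and the unadjusted test as a sensitivity analysis. State this before 1-year results are compared by arm.

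If this model is to carry the non-inferiority claim, fix a margin in IQ points in advance, since the 10% limit cannot be applied to a difference in means. If the claim stays on the proportion who decline, say so and present the adjusted IQ difference beside it.

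Cost: a change of wording, up to two degrees of freedom, a check that dominance is recorded in the RF-TC arm, and the work of justifying a margin on the IQ scale. No further patients or IQ assessments are needed.

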### Patient and public involvement

We are here to state that the patients or public were not involved in the design of our research. If any harm exists, the health and surgery insurance will cover the indemnity to the patients. The protocol and the design of this study were discussed and developed by MDT including neurologists, neurosurgeons, neuroimaging physicians, and neuropsychology physicians.

### Ethical considerations and result dissemination

Written informed consent will be obtained from all participants and their representatives. The STARTS protocol has been approved by the ethics committee at Xuanwu Hospital and will be conducted in accordance with the Declaration of Helsinki. The data monitoring committee will consist of one neurosurgeon and two neurologists independent from this study. If there exists any modification, the changes should be submitted to the ethics committee and the study approval department. Unless approved, all the modifications should not be made. STARTS is also registered at the US National Institutes of Health (ClinicalTrials.gov: NCT03941613, registered on May 8, 2019). The schedule and the results of this study will be open on the ClinicalTrials.gov website and will also be open to peer-reviewed journals. If possible, the results will be shown at the national conference and will be further discussed accompany with specialists on the same research field. All information including identity, medical history, illness, medical examination, and laboratory results will be kept strictly confidential within the limits of the law. Unless authorised, the ethics committee and the study approval department may have access to the medical records related to this study to verify the authenticity and accuracy of the data collected from this study, with no personal details involving. All the participants’ personal information will be confidential to the public and journal.

## Discussion

RCTs are considered the most reliable form of scientific evidence given their ability to reduce spurious causality and bias. However, to our knowledge, the present study is the first RCT to compare cognitive outcomes and treatment results between SEEG-guided RF-TC and standard ATL for mTLE.

ATL has been considered an effective treatment for temporal lobe epilepsy and is now the most commonly used surgical technique for mTLE patients. Long-term seizure-free rates for ATL range from 59 to 80% [23]. However, previous studies have reported that ATL for mTLE is associated with complications such as memory impairments and visual field deficits [9, 20]. A systematic review by Sherman et al. noted verbal memory decline in up to 44% and 20% of patients undergoing dominant and non-dominant hemisphere ATL, respectively [24]. Given that SEEG-guided RF-TC may ensure better preservation of cognitive function and reduce the risk of visual field impairments, RCTs evaluating such treatment are required.

SEEG is a minimally invasive method for precisely localising the seizure-onset zone that is advantageous due to its ability for a three-dimensional definition of the epileptogenic zone [25]. Although SEEG-guided RF-TC has been used for typical cases of hypothalamic hamartoma, periventricular nodular heterotopia (PNH), and mTLE with or without hippocampal sclerosis, treatment outcomes have varied across studies, and the efficacy of RF-TC for mTLE remains controversial [13, 14, 16, 18]. Moles et al. compared postoperative seizure outcomes between SEEG-guided RF-TC and ATL, reporting that none of the patients in the SEEG-guided RF-TC group achieved seizure freedom. In contrast, 37 patients (75.5%) in the ATL group were seizure-free 12 months after treatment [12]. In a review of their series, Malikova et al. found that nearly 70% of patients were seizure-free postoperatively, similar to findings in our unpublished study [22]. Given these discrepancies, RCTs are also required to verify the non-inferiority of SEEG-guided RF-TC when compared with ATL.

Limitations of the study include the strict eligibility criteria which may lead the difficulty for the participant enrolment. Secondly, as we focused only on mTLE with hippocampal sclerosis patients, other types of temporal lobe epilepsy (such as neocortical temporal lobe epilepsy) will not be investigated in this study and further research may be promoted.

## Trial status

Recruitment ongoing (approximate recruitment completed date: February 28, 2021).

## Data Availability

The datasets used and/or analysed during the current study are available from the corresponding author on reasonable request.

## Abbreviations

EEG: Electroencephalogram
mTLE: Mesial temporal lobe epilepsy
ATL: Anterior temporal lobectomy
RF-TC: Radiofrequency thermocoagulation
SEEG: Stereotactic electroencephalography
RCT: Randomised controlled trial
MDT: Multidisciplinary team
AEDs: Antiepileptic drugs
I.Q.: Intelligence quotient
MRI: Magnetic resonance imaging
PET: Positron emission tomography
WAIS-IV-C: Wechsler Adult Intelligence Scale-IV
WCIS-IV-C: Wechsler Children’s Intelligence Scale-IV
QOLIE-89: Quality of Life in Epilepsy-89 scale
QOLIE-48: Quality of Life in Epilepsy-48 scale
CRF: Case report form
PNH: Periventricular nodular heterotopia
